## 3. Materials and Methods

### 3.1. Study Design and Ethical Approval

We plan a 12-week single-center, double-blind dietary intervention in which AIDH patients will be randomly allocated into two groups: experimental and control. Participants in the experimental group will receive individual personalized nutrition education along with the probiotic *Lactiplantibacillus plantarum 299v*, while in the control group, *Lp299v* will be replaced by a placebo. The form of the administered supplement (capsule) will be identical in both cases; neither the researcher nor the patient will have knowledge of its contents. The detailed schedule of the trial is presented in the following section. All visits for measurements and data collection will take place at the Dietetics Counselling Center, Department of Dietetics, Faculty of Human Nutrition, Warsaw University of Life Sciences. All tests performed during the intervention will be provided free of charge to the participants, who will not receive any financial benefits or cost reimbursements for participating in the study.

The study protocol was registered with and approved by the Ethics Committee for Research with Human Participation at the Institute of Human Nutrition Sciences, Warsaw University of Life Sciences, in compliance with the principles of ethics (Resolution No. 22/2021 and No. 21/2022). The study will adhere to the Declaration of Helsinki, and all participants will provide informed consent. Each participant will be presented with a detailed description, and any questions or concerns will be addressed. Participants will be informed that they may withdraw at any stage from the study without providing a reason. It is important to note that side effects of *Lactiplantibacillus plantarum 299v* are rare and do not pose a threat to the patient. To ensure participant retention, direct contact with the researcher will be available throughout the study period.

### 3.2. Selection of Participants

The selection of the sample for the study will be purposive, taking into account the inclusion and exclusion criteria. Recruitment for the study will be carried out using the snowball method, mainly via social networking sites (i.e., internet websites associated with Hashimoto’s patients). Additionally, collaboration with medical facilities and pharmacies will be established to reach a broader pool of potential participants. The CAWI (Computer-Assisted Web Interview) and PAPI (Paper and Pen Personal Interview) methods will be used for collecting data.

The inclusion criteria will be a medical diagnosis of Hashimoto’s disease based on anti-TPO, anti-TG, or an ultrasound image characteristic of AIDH; thyroid function status (euthyroid, hypothyroidism); female; age in the range of 18-64 years; normal body weight (body mass index BMI 18.50–24.99 kg/m^2^) or excessive body weight (BMI ≥ 25.00 kg/m^2^); and/or low-quality diet (low Pro-Healthy Diet Index (pHDI-10)) [36]. Women with contraindications to a body composition analysis performed using the electrical bioimpedance method (i.e., having a pacemaker) will also be included. However, for these patients, the body composition analysis stage will be skipped.

The exclusion criteria will be thyroid diseases other than AIDH, pregnancy, lactation, diagnosed cancer, and lack of consent to participate in the study. The individual must not take *Lp299v* or medications for weight loss or be diagnosed with celiac disease, Duhring’s disease, or a gluten allergy. The minimum number of subjects (47 for each group) was calculated based on an expected 50% improvement in the overall quality of life after 12 weeks of the intervention in the experimental group, with an assumed 5% significance level and 80% power. The baseline sample size of 100 patients was established to account for potential participant withdrawals.

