## 1. Introduction

The autoimmune disease of hypothyroidism (AIDH, Hashimoto’s thyroiditis) affects an increasing number of people, particularly women [1]. In the course of this disease, many symptoms and health consequences arise that worsen the quality of life [2]. Hypothyroidism worsens the motility of the gastrointestinal tract, which may lead to disorders such as dyspepsia, IBS (irritable bowel syndrome), or SIBO (Small Intestinal Bacterial Overgrowth) [3,4]. Hypothyroidism may also increase the risk of obesity [5], which is associated with a positive anti-TPO (antibodies directed against thyroid peroxidase) titer [6]. Patients with AIDH are more likely to have excess body mass compared to those without the disease [5], which increases the risk of hypertension—the most important risk factor for ischemic heart disease, stroke, other cardiovascular diseases, chronic kidney disease, and dementia [7]. On the other hand, subclinical hypothyroidism may also occur during the course of AIHD, increasing the risk of hypertension, especially in middle-aged women, although the mechanism is not fully understood [8]. The treatment for AIHD mainly involves the patient taking levothyroxine for life [2].

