### 3.3. Randomization and Blinding

Participants will be randomly allocated, according to a generated randomization list, to the experimental group (approximately *n* = 50) or the control group (approximately *n* = 50). The randomization list will be generated by a researcher who is not involved in the experiment. The study is designed as double-blinded, meaning that neither the participant nor the intervention conductor will be aware of which group is the experimental group (receiving *Lp299v*) and which is the control group (receiving placebo) until the end of the experiment. Each patient will be assigned a unique code number, which will be used to label all results to maintain blinding.

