### 3.11. Nutrition Education

Nutrition education is planned for 12 weeks, with 6 individual meetings spaced about 2 weeks apart. There will be a total of 6 h of education in the entire program. The form of meetings will be online or in person, depending on the patient’s preferences. At the beginning of the education intervention, the patient will be presented with an interpretation of her eating habits, the nutritional value of her diet, and her nutritional status. A personalized goal (e.g., weight loss in the case of a patient with obesity) that the patient should achieve will also be discussed and set. During the education intervention, the following issues, among others, will be discussed with all participants: nutritional recommendations and essential nutrients (role, sources in food) in Hashimoto’s thyroiditis; factors affecting iron bioavailability; glycemic index and glycemic load—application and importance; weight reduction assumptions; snacking—causes and tips on how to minimize the need to reach for snacks; mindful eating; “Healthy eating plate”—nutritional recommendations for the Polish population presenting the correct proportions of individual product groups in a daily diet [53]; interactions between levothyroxine and food; the importance of microbiota in HT; *Lactobacillus plantarum 299v*—impact on human health based on scientific research (mainly on the immune system, iron, intestinal symptoms, blood pressure); and myths and facts about nutrition in HT. In addition to the above-mentioned topics, participants will be able to receive answers to individual questions/concerns.

All educational materials will be prepared based on the scientific literature and standards by The Polish Society of Dietetics and the National Public Institute—National Institute of Hygiene. Each participant will receive educational materials and a sample menu depending on energy needs to illustrate how meals and portions should look. Throughout the entire study period, participants will have the possibility of consulting with a dietitian, who will also support the introduction of changes in eating habits depending on individual personalized needs.

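### Euthyroid and hypothyroid women enter regardless of recent levothyroxine changes and thyroid function is not followed, which adds noise between arms and confounds the within-arm changes used to judge counselling

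*Protocol article*

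**What the plan says.** All references are to the protocol article.

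- **Entry (3.2).** Eligibility lists "thyroid function status (euthyroid, hypothyroidism); female; age in the range of 18-64 years". Thyroid-related exclusion is limited to other thyroid disease: "The exclusion criteria will be thyroid diseases other than AIDH, pregnancy, lactation, diagnosed cancer, and lack of consent to participate in the study". The medicine and supplement restriction reads "The individual must not take *Lp299v* or medications for weight loss". Nothing is said about levothyroxine being absent, new, under adjustment or unchanged.
- **Allocation (3.3).** "Participants will be randomly allocated, according to a generated randomization list", about 50 per arm, double-blind. No stratification factor is named.
- **Background (1).** Treatment "mainly involves the patient taking levothyroxine for life". "Hypothyroidism may also increase the risk of obesity", and in the course of the disease "many symptoms and health consequences arise that worsen the quality of life".
- **Objectives (2).** The primary outcomes are body weight and quality of life. The secondary objective and the first hypothesis concern the effect of nutrition counselling itself.
- **Measurements (3.4, 3.10).** Assessment is at baseline and 12 weeks. Anti-TPO is the only blood test; no thyroid function measure is listed.
- **Medication data (3.6).** Participants are asked about medical care and medicines. No rule is given for a change in levothyroxine, and 3.13 names no use of the answers.
- **Education (3.11).** Six meetings about two weeks apart, in both arms, with topics that include "interactions between levothyroxine and food".
- **Analysis (3.13).** Changes from baseline are tested with a dependent-samples t-test when normally distributed; group differences are examined by multivariate analysis of variance.

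**The concern.** By the protocol's own account, hypothyroidism bears on weight, and the disease bears on quality of life. A woman whose levothyroxine was started or altered near baseline may therefore change on both primary outcomes over 12 weeks for reasons unrelated to diet or Lp299v. She enters the same comparison as a woman on long-settled treatment, and the outcome set holds nothing that would show the difference. The protocol bars weight-loss medicines and handles biotin interference with the anti-TPO assay (3.10), yet leaves open changes in the standard treatment of the disease itself.

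Two inferences are exposed, to different degrees. The Lp299v-placebo contrast could lose precision. The counselling objective is more exposed: both arms are counselled, so counselling can be judged only from change over time, and randomisation does not protect that.

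**Working it through.** **1. The plan's own figure.** Section 3.2 gives 47 per group for 5% significance, 80% power and a 50% improvement in quality of life, without a control value, SD or responder rate. The figure cannot be reproduced from those inputs alone. Back-solving for two means, two-sided:

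SMD = (1.960 + 0.842) × √(2/47) = 0.578.

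This is used below only as a reference effect at which 47 per arm has 80% power. The point does not depend on it.

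**2. Assumptions not in the documents.** A share f of women in each arm has a treatment-driven improvement of m SD over 12 weeks, where the SD is that of change among the other women. All such changes go in the same direction. The range is f = 0.1-0.5 and m = 0.5-1.

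**3. Formulas.**

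- Added variance: v = f(1 − f)m².
- Between-arm power: Φ(0.578 / √[(1 + v) × 2/47] − 1.960).
- Within-arm test when education has no effect: t = fm√47 / √(1 + v), and rejection probability = 1 − Φ(1.960 − t) + Φ(−1.960 − t).

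| f | m | v | Between-arm power | Within-arm rejection (nominal 0.05) |
|---|---|---|---|---|
| 0.1 | 0.5 | 0.023 | 79.1% | 0.063 |
| 0.1 | 1 | 0.090 | 76.5% | 0.101 |
| 0.2 | 0.5 | 0.040 | 78.4% | 0.103 |
| 0.2 | 1 | 0.160 | 73.9% | 0.247 |
| 0.3 | 0.5 | 0.052 | 78.0% | 0.171 |
| 0.3 | 1 | 0.210 | 72.1% | 0.464 |
| 0.5 | 0.5 | 0.062 | 77.6% | 0.383 |
| 0.5 | 1 | 0.250 | 70.7% | 0.866 |

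**4. Simulation check.** In 20,000 trials with 47 per arm, f = 0.3 and m = 1, between-arm type I error was 0.0496 and within-arm rejection was 0.447. The second agrees with the approximate 0.464.

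**5. Chance imbalance.** With 50 per arm and 20% of women on changing treatment, the arms differ by 5 or more such women with probability 0.26, and by 8 or more with probability 0.06.

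**6. The same effect in ThyPRO points.** Assume 10-30% of women improve 10 points more than the rest. The 95% range of the resulting shift in the arm difference is ±1.96 × √(2q(1 − q)/50) × 10, which is ±1.18 points at q = 0.1 and ±1.80 at q = 0.3. The added variance is 100q(1 − q), which is 9 and 21 points². These are one quantity in two forms: 1.96 × √(2 × 9/50) = 1.18 and 1.96 × √(2 × 21/50) = 1.80. They must not be added together.

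**The case against.** The strongest reply is that the trial is randomised, double-blind and placebo-controlled. Chance imbalance in treatment changes is already carried by the standard error, and type I error stays at 5%. This stands. A reader might infer that the Lp299v effect is biased; the documents do not support that.

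A reader might also infer that chance imbalance could match a plausible probiotic effect. No such effect is given in points. Taking the reference SMD of 0.578 and an assumed SD of 10-20 points, the planned difference is about 5.8-11.6 points, so a 1.8-point shift is roughly 16-31% of it.

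Other parts of the reply that stand:

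- Entry is not open to any thyroid function; only euthyroid and hypothyroid status are listed.
- Medicines are already asked about in 3.6. What goes unmeasured is thyroid function.
- Levothyroxine-food teaching is given to both arms. Better levothyroxine-taking that follows from it is an effect of the education, not contamination.
- The absence of an uneducated comparator would weaken within-arm inference even if every woman's treatment were settled.
- An article may condense its randomisation details, so silence on stratification is weak evidence on its own.

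What the reply does not answer is that eligibility and outcomes are set out here in detail and leave treatment changes neither restricted nor followed, while one objective rests on uncontrolled 12-week change.

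**Conclusion.** The point holds, with moderate weight. For Lp299v against placebo the cost is precision: power of about 71-79% instead of 80% over the assumed range, with no systematic bias. For counselling the cost is interpretive. A within-arm 12-week change could partly reflect levothyroxine changes, and the paired test could reject with probability between 0.06 and 0.87 when education does nothing. The planned correlations of nutrient change with change in anti-TPO and quality of life (Strengths and Limitations) are open to the same confounding.

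The documents give neither the share of women whose treatment changes nor the size of the resulting shift, so these figures illustrate a range and are not estimates. If treatment changes moved outcomes in both directions, the within-arm distortion would be smaller. It would be wrong to conclude that any within-arm improvement is treatment adjustment; the documents support only that the two could not be told apart.

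**What to change.** 1. **Allocation and analysis (3.3, 3.13).** Stratify the randomisation list by baseline thyroid status, which is an eligibility item, and baseline levothyroxine use, which is already asked in 3.6. At the least, adjust the primary between-arm comparison for both. This removes baseline differences only; it does not capture changes during the 12 weeks.
2. **Recording (3.11, 3.12).** At the existing two-weekly meetings, where capsule use and side effects are already asked about, also record any start or change of levothyroxine. Report these by arm.
3. **Sensitivity analysis.** Repeat the primary comparison without women whose treatment changed, labelled as supportive only. It conditions on an event after randomisation, and the Discussion itself suggests a route from Lp299v through iron to thyroid hormone.
4. **Interpretation.** Rest Lp299v conclusions on the between-arm contrast. Do not attribute within-arm change to counselling alone.
5. **Eligibility (3.2).** The investigators should consider whether entry requires levothyroxine treatment, including no treatment, to be unchanged before baseline. Whether to do so, and for what period, is their decision.
6. **Limitations.** State that, without a thyroid function assay, shifts in thyroid function itself stay unmeasured.

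Items 1 to 4 and 6 cost a change to the list or model, one question per meeting and some text; no new assay is needed. Item 5, if adopted, would make the recruitment pool somewhat smaller or slow enrolment.

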## 2. Study Aim and Hypothesis

The primary objective of the trial is to assess the effect of a dietary intervention with probiotic *Lp299v* supplementation on body weight and quality of life in female AIDH patients.

The secondary objective of the trial is to evaluate the effectiveness of individual personalized nutritional counseling on several key parameters among patients diagnosed with Hashimoto’s thyroiditis. The specific focus areas for assessment include food selection and diet quality, body composition, serum anti-TPO, and blood pressure.

The research hypotheses are as follows:-Individual personalized nutrition education aimed at improving food selection and diet quality may enhance nutritional status, anti-TPO parameters in the blood, and the overall quality of life in AIDH patients.-The *Lp299v* strain may augment the impact of the individual nutritional intervention, particularly in terms of improving the quality of life, body weight status, and anti-TPO parameters in the blood.

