To assess the overall quality of the diet, the following Polish-validated tools will be used: the Pro-Health Diet Index (pHDI-10) and the non-Healthy-Diet Index (nHDI-14) [36]. The first one includes ten food items: whole-grain bread/rolls, coarse-grounded groats, milk, fermented milk beverages, fresh cheese curd products, white meat, fish, legume-based foods, fruit, and vegetables. The latter includes fourteen food items: white bread and bakery products, white rice and fine-ground groats, fast foods, fried foods, butter, lard, cheese, cured meat/smoked sausages/hot dogs, red meat, sweets, tinned meats, sweetened beverages, energy drinks, and alcohol. Based on the answers provided by each individual, the total points are recalculated to a range of 0%–100% according to the questionnaire’s manual. The index value reflects the intensity of beneficial or harmful characteristics for health. For example, pHDI-10 scores ranging from 0 to 33 indicate low diet quality [36].

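### The 'and/or' in the BMI and diet inclusion rule defines two different trial populations, and body weight, part of the primary objective, is sensitive to which one is recruited

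*Protocol article*

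**What the plan says.** Section 3.2 of the protocol article lists, after diagnosis, thyroid status, sex and age, two BMI ranges: "normal body weight (body mass index BMI 18.50–24.99 kg/m^2^) or excessive body weight (BMI ≥ 25.00 kg/m^2"). It then adds "and/or low-quality diet (low Pro-Healthy Diet Index (pHDI-10"). Section 3.5 gives the diet cut-off: "pHDI-10 scores ranging from 0 to 33 indicate low diet quality", on an index rescaled to 0–100%. The exclusions in section 3.2 begin "The exclusion criteria will be thyroid diseases other than AIDH, pregnancy, lactation, diagnosed cancer, and lack of consent to participate in the study". They go on to Lp299v use, weight-loss medication, celiac disease, Duhring's disease and gluten allergy. None refers to underweight.

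Section 2 states the primary objective as the effect of the intervention with "supplementation on body weight and quality of life in female AIDH patients", without restriction by BMI. Section 3.11 sets goals woman by woman: "A personalized goal (e.g., weight loss in the case of a patient with obesity") is the example given. Section 3.3 says "Participants will be randomly allocated, according to a generated randomization list" and mentions no strata. Section 3.13 compares the two groups as wholes.

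**The concern.** The connector decides who may enter, and it can be read in two ways. A screener faced with a normal-weight woman whose pHDI-10 is above 33 cannot tell from the text whether she is eligible. Nor can the screener tell whether an underweight woman with a low score is eligible. This is a rule that the article states and fixes badly, not a detail left to another document.

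Body weight makes the choice matter. The mix of BMI classes affects how much weight women are expected to lose under the education that both groups receive, and in whom a loss counts as an improvement. A wide mix adds between-woman variation to the weight comparison unless BMI is taken into account in the design or the analysis.

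**Working it through.** **Step 1. The two readings.** Inputs: the BMI ranges and connector in section 3.2, and the low cut-off of 0–33 in section 3.5. Let B mean BMI of 18.50 or more (18.50–24.99 joined to 25.00 and above leaves no gap at the two decimals used). Let L mean a low pHDI-10.

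| BMI class | pHDI-10 | 'B and L' | 'B or L' |
|---|---|---|---|
| <18.50 | low | no | yes |
| <18.50 | not low | no | no |
| 18.50–24.99 | low | yes | yes |
| 18.50–24.99 | not low | no | yes |
| ≥25.00 | low | yes | yes |
| ≥25.00 | not low | no | yes |

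'And' gives 2 of 6 cells and 'or' gives 5 of 6. The BMI ranges alone give 4 of 6. Under 'or', the diet criterion therefore adds exactly one cell, underweight with a low score. The only cell removed is underweight with a score that is not low. These are counts of cells, not of women; the documents give no distribution of BMI or pHDI-10.

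**Step 2. The plan's own sample size.** Section 3.2 gives 47 per group for a 50% improvement in quality of life, at 5% significance and 80% power. It states no SD and no control-group value, so 47 cannot be reproduced from the article. Solved backwards, two-sided, by the normal approximation:

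d = (1.960 + 0.842) × √(2/47) = 0.578.

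This d is used below only as a scale on which 47 per group has 80% power. It is not a body-weight effect; the article gives none.

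**Step 3. What ignoring BMI class costs in precision.** Assume that the probiotic effect is the same in all women, that the within-class SD of weight change is 1, that a share f of women belong to one class, and that mean change differs between the classes by D in both groups. Then

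unadjusted SD = √(1 + f(1 − f)D²), and power = Φ(0.578 × √(47/2) / SD − 1.960).

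With f = 0.5:

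- D = 0.5: SD = √1.0625 = 1.031, power 78%.
- D = 1: SD = √1.25 = 1.118, power 71%.
- D = 1.5: SD = √1.5625 = 1.25, power 61%.

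For D = 1, 0.578 × 4.848 / 1.118 = 2.506; 2.506 − 1.960 = 0.546; Φ(0.546) = 0.71. Including BMI class in the analysis removes this extra variance and returns power to about 80% on the same scale. Neither f nor D is in the documents.

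**Step 4. Would it be better to analyse weight only at BMI ≥25?** Take 47 per group, the two-sample t-test value d = 0.584 that gives 80% power, and a share q of normal-weight women (assumed).

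| q | Pooled, no effect in normal-weight women | BMI ≥25 only | Pooled, equal effect in all |
|---|---|---|---|
| 0.3 | 50% | 65% | 80% |
| 0.4 | 39% | 58% | 80% |
| 0.5 | 29% | 50% | 80% |

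The first column uses an SMD of 0.584(1 − q) with n = 47; the second uses 0.584 with n = 47(1 − q). Pooling matches the restricted analysis once normal-weight women show about 44%, 42% or 40% of the effect seen at BMI ≥25 (q = 0.3, 0.4, 0.5). Which analysis is better depends on an effect pattern that the article does not give.

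**The case against.** The strongest reply is that broad eligibility is a legitimate choice. Quality of life is also in the primary objective and is the outcome on which the trial was sized, and normal-weight women are relevant to it and to anti-TPO. The explicit floor of 18.50 suggests that underweight women were not meant to enter. Figure 1, which is not shown, may settle the connector, since its legend defines pHDI-10. Strata and covariates are details that an article commonly leaves to the full protocol or the SAP. All of this is fair, and the silence on stratification is not raised as an omission. But the eligibility text is stated, and it should not need a figure to be understood. If the floor was intended, 'or' undoes it for women with a low score.

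Several stronger readings are tempting and do not hold:

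- A reader might infer that the trial excludes almost nobody. That would describe only the BMI and diet line read as 'or'. Diagnosis, sex, age, pregnancy, lactation, cancer, medication and the gluten-related conditions still select.
- A reader might infer that pooling BMI classes biases the weight result. It does not. Both groups receive the same education, allocation is random, and chance imbalance in BMI is already part of the sampling variance.
- A reader might infer that weight should be analysed only at BMI ≥25. Step 4 shows a trade-off: power falls from 80% to 65%, 58% or 50% if the effect is the same in all women. Section 2 expects a benefit for body weight status without a BMI limit.
- A reader might infer that women whose score is not low have no room to improve. Low covers only 0–33 of 100, and nHDI-14 is a separate index.
- A reader might infer that weight content is reserved for women with obesity. Section 3.11 gives weight loss as an example of a goal and lists weight reduction among topics for all participants.

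**Conclusion.** The point holds as a defect in the stated inclusion rule. The two readings admit 5 of 6 and 2 of 6 BMI-by-diet cells, and nothing in the article's text chooses between them. That conclusion is pure logic and rests on no assumed figure. How many women it affects is unknown.

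The recommendation on stratification and adjustment is secondary. It rests on the expectation that weight change under the education differs by BMI and goal, which personalized goals make plausible but which the documents do not quantify. Its size, about 12% on the SD and 80% power falling to about 71%, holds for an assumed 1 SD difference between equal-sized classes; over differences of 0.5 to 1.5 SD, power is 78% to 61%. The point should be acted on because the rule governs entry and the correction is cheap. It does not threaten the validity of the randomized comparison.

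**What to change.** 1. Replace 'and/or' in section 3.2 with explicit logic that answers two questions: whether a low pHDI-10 (0–33) is required, and of whom; and whether women with BMI below 18.50 are eligible. The choice is the sponsor's; make sure Figure 1 and the screening form agree with it.
2. Stratify the randomization list by BMI below 25 versus 25 and above. If the list is already in use, keep it and rely on step 3.
3. Compare body weight between groups in all randomized women, with the BMI stratum, or baseline weight or BMI, in the model. Report results by BMI class as supportive.

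The cost is one rewritten eligibility line, a list with two strata and one sentence in the analysis section. No extra participants or measurements are needed, since weight and height are already taken at baseline; they must be available before allocation if the list is stratified. Requiring a low-quality diet would narrow the recruitment pool; keeping the wide reading would not.

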### 3.7. Quality of Life

The quality of life of the participants will be assessed using the Quality of Life Questionnaire for Patients with Thyroid Diseases (ThyPROpl).

ThyPROpl is a thyroid-specific questionnaire validated for the Polish population by Sawicka-Gutaj et al. [38]. The questionnaire comprises 85 questions grouped into 13 scales measuring aspects of quality of life relevant to thyroid patients. The 13-point scale includes questions on (1) symptoms, (2) feeling tired, (3) energy, (4) memory and concentration, (5) nervousness and tension, (6) mental well-being, (7) problems with coping or mood swings, (8) relationships with other people, (9) daily activities, (10) sex life, (11) the impact of the disease or its treatment on appearance, (12) the intensity of the impact of the disease on the subject in general. All quality-of-life questions will cover the last 4 weeks prior to the survey. The respondents must choose 1 of 5 answer categories: (1) not at all, (2) a little, (3) average, (4) quite a lot, (5) very much. In the question regarding difficulties in performing duties at work, the authors added an additional category—“I do not work” [38]. The score ranges from 0 to 100, with higher scores indicating a poorer quality of life.

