### 3.13. Statistical Analyses

All statistical analyses will be conducted using Statistica 13.1 PL (StatSoft Inc., Tulsa, OK, USA; StatSoft, Krakow, Poland). Categorical variables will be presented as a sample percentage (%). Continuous variables will be presented as means with 95% confidence intervals (95%CIs) for variables with a normal distribution or medians with an interquartile range (IQR) for variables with a non-normal distribution. To assess the impact of the nutritional intervention with probiotic supplementation and verify the differences between the experimental and control groups, multivariate analysis of variance and two-tailed tests will be applied. The normality of the variable distribution will be assessed using the Shapiro–Wilk test before statistical analysis. For continuous variables, e.g., diet quality scores, scores of quality of life, markers of adiposity, metabolic parameters, and changes after 12 weeks of education relative to baseline, will be assessed using a *t*-test for dependent samples for normally distributed variables or a Mann–Whitney test for variables without a normal distribution. Differences in categorical variables will be examined using the Pearson chi-squared test. *p* < 0.05 will be considered statistically significant.

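### The stated basis for 47 per group, a 50% improvement in the experimental arm, does not support 80% power for the probiotic-versus-placebo comparison

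*Protocol article*

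**What the plan says.** Section 3.2 (Selection of Participants) states "The minimum number of subjects (47 for each group" and describes this figure as "calculated based on an expected 50% improvement in the overall quality of life after 12 weeks of the intervention in the experimental group". It assumes a 5% significance level and 80% power. It then adds: "The baseline sample size of 100 patients was established to account for potential participant withdrawals".

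Other sections bear on this sentence:

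- Section 3.1 randomises women to education plus Lp299v or education plus placebo. Section 3.11 describes one education programme for all participants.
- Section 2 names quality of life, with body weight, in the primary objective. Its first hypothesis is that the education "may enhance nutritional status, anti-TPO parameters in the blood, and the overall quality of life in AIDH patients". Its second is that Lp299v may add to that effect.
- Section 3.7 describes the outcome, ThyPROpl: "The score ranges from 0 to 100, with higher scores indicating a poorer quality of life".
- Section 3.13 aims to assess the intervention and "verify the differences between the experimental and control groups"; for this purpose it says that "multivariate analysis of variance and two-tailed tests will be applied". It also plans a dependent-samples t-test for changes from baseline.

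The article gives no expected control-arm result, between-arm difference, SD or baseline ThyPROpl score, and does not say which test the sample size was computed for.

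**The concern.** The power of a two-arm comparison is set by the difference between the arms relative to its variability. The only effect the protocol states is an improvement in one arm. That improvement combines three things: the response to education, any response to taking a capsule, and the effect of Lp299v. The first two are also present in the control arm. On the protocol's own first hypothesis the control arm should improve, so the probiotic effect would be smaller than the whole 50%.

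Quality of life is the only outcome named in the sample-size sentence, so readers will take the 80% as the power to detect an effect of Lp299v on it. If the real power for a modest added benefit is much lower, a null result could be misread as evidence that the strain does nothing.

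**Working it through.** **Inputs from the article.** Two-sided α = 0.05 (5% in Section 3.2, two-tailed tests in Section 3.13); power 80%; 47 per group; a 50% improvement in the experimental group. The expected control result and the SD are not given.

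**1. Can 47 be reproduced?** Not from these inputs alone, because a sample-size formula for two groups needs a between-arm difference and an SD, or two response rates. One can only solve backwards for assumptions that return about 47.

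*Means.* n per arm = 2(z₀.₉₇₅ + z₀.₈₀)²/d², where d is the between-arm difference in SD units. With n = 47, d = √2 × (1.960 + 0.842)/√47 = 0.578. The t-distribution version gives 0.584. Both round to 0.58 SD.

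*Responder rates* (pooled variance under the null, no continuity correction): n = [z₀.₉₇₅√(2p̄(1−p̄)) + z₀.₈₀√(p₁(1−p₁) + p₂(1−p₂))]²/(p₁−p₂)².

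| Experimental | Control | n per arm (rounded up) |
|---|---|---|
| 50% | 22% | 45 |
| 50% | 23% | 49 |
| 50% | 25% | 58 |
| 81% | 54% | 47 (46.04 before rounding) |

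The last row is a 50% relative gain over control (1.5 × 54% = 81%).

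*Paired change within one arm.* n = (z₀.₉₇₅ + z₀.₈₀)²/d², so 47 corresponds to a standardised change of 2.802/√47 = 0.409.

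Several different assumptions therefore lead to 47, and none of them is in the article.

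**2. What follows if the 50% is a total within-arm change?** Suppose 47 was obtained by treating the experimental arm's change as if it were the between-arm difference. The change would then be 0.584 SD, and any control improvement has to be subtracted. The control fractions below are assumptions chosen to show the sensitivity (two-sample t-test, 47 per arm, two-sided 5%).

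| Control change as a share of experimental | Between-arm difference (SD) | Power |
|---|---|---|
| none | 0.584 | 80% |
| one third | 0.389 | 46% |
| one half | 0.292 | 29% |
| two thirds | 0.195 | 15% |

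On a responder reading with 50% in the experimental arm, power at 47 per arm also depends wholly on the assumed control rate: 87% at 20%, 71% at 25%, 51% at 30%, 31% at 35% and 16% at 40%.

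If 47 came from the paired calculation (0.409), and the same SD applies between arms, between-arm power is 51% with no control change and 17% if controls achieve half the change.

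**3. What 47 per arm can detect.** At 80% power, about 0.58 SD without baseline adjustment. With adjustment for the baseline score the figure is multiplied by √(1−r²). For an assumed baseline-to-week-12 correlation r of 0.5 this is 0.584 × 0.866 = 0.51 SD; for r of 0.7 it is 0.584 × 0.714 = 0.42 SD. The article gives no value for r.

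**4. Withdrawals.** 2 × 47 = 94, raised to 100, leaves room for 6% loss (47/0.94 = 50 per arm).

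**The case against.** The strongest reply is that the article never says the calculation was done within one arm. A number given for each group fits a two-sample formula, and the sentence may report only the experimental half of a two-group assumption. The reading of 81% against 54% responders even allows a high control response, consistent with education helping both arms. A condensed article may also leave the control assumption and SD to a fuller document.

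Much of this stands. A reader might infer that the 80% power is false, or that the trial is underpowered. The documents do not support that, because unstated between-arm assumptions can return 47 with full power. A reader might also take the 50% as a standardised effect of 0.5, which would need 64 per arm. Nothing in the text equates the two. The control fractions and response rates used above are not from the protocol either, so the resulting power figures illustrate sensitivity and do not estimate this trial's power.

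What does not stand is the view that this is only missing detail. The article does state a basis for its sample size and power, and that basis is a one-arm change, which is the wrong quantity for the comparison it plans. A fuller document could supply the between-arm assumption, but the printed justification would still need correcting.

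**Conclusion.** The point holds in a limited form. The 80% power for Lp299v against placebo does not follow from the basis given in Section 3.2, and 47 per group cannot be derived from it. The number fits unstated assumptions such as a between-arm difference of about 0.58 SD, 50% against about 22–23% responders, or 81% against 54%.

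If the 50% is a total within-arm change that was used to size the trial, power for the probiotic effect is below 80% and falls as control improvement rises. The size of the shortfall cannot be fixed from the documents, because it depends on a control response that they do not give. Whether the calculation was within-arm or between-arm is not settled.

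**What to change.** Keep N=100 and replace the sample-size sentence in Section 3.2 with a between-arm statement.

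- If a between-arm assumption was used, state it: the expected difference with its SD, or the two responder rates, together with the test and its sidedness.
- If not, state that 47 evaluable women per arm give 80% power, at a two-sided 5% level, for a between-arm difference of about 0.58 SD in ThyPROpl. This reports what the sample can detect. It does not show that such a difference is plausible or important, and the text should not suggest that it does.
- In either case, remove the claim that 80% power follows from a 50% improvement in the experimental arm.
- Quote a smaller detectable difference (about 0.51 to 0.42 SD for an assumed correlation of 0.5 to 0.7) only if a baseline-adjusted analysis is adopted, and label the correlation as an assumption.

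The cost is one rewritten sentence, with no extra patients and no change to procedures. The downside is that the stated power claim becomes less favourable.
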